### Definitions

Culture of *M. tuberculosis* will be considered to be converted to negative when two or more consecutive cultures, taken at different visits, are found to be negative in liquid medium. When a participant cannot produce sputum after the first negative culture sputum, they will be considered as having achieved culture conversion. The submission date of the first confirmed negative sputum culture will be regarded as the date of culture conversion. If *M. tuberculosis* is found to be re-cultured two or more times following a negative culture conversion, this will be termed culture reversion [18]. Treatment success is defined as achieving negative culture conversion and maintaining negative cultures till the end of treatment.

The sum of treatment failure, recurrence, death during treatment (except for accidents and suicide), loss to follow-up, and withdrawal from the study will be designated as “unfavorable outcomes.” Treatment failure will be defined as participants who fail to achieve culture conversion during treatment period, or as participants using second-line anti-TB drugs for more than 4 weeks. Recurrence will be assigned to participants that indicate the presence of *M. tuberculosis* in sputum cultures for two or more times after the end of treatment.

Adverse events will be defined when undesirable medical events have occurred in participants, irrespective of a causal relationship with the treatment [19]. When adverse events result in death, life-threatening conditions, patient hospitalization or prolongation of existing hospitalization, persistent or significant disability or incapacity, or a congenital anomaly or birth defect, the events will be classified as serious adverse events. The severity of each adverse event will be assessed based on Common Terminology Criteria for Adverse Events (CTCAE) version 5.0 [20].

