### Sample size calculation

The objective of this study is to determine whether the new regimen is non-inferior to the existing standard treatment. The primary outcome is an unfavorable treatment outcome at 18 months after randomization. Based on the existing study [21], a 10% unfavorable treatment outcome for the standard treatment (control group) and a 0% difference from the investigational group is assumed. To obtain a study with 80% power and a 2.5% one-sided significance level for the non-inferiority recognition limit of 6%, each group will contain 393 participants. Assuming a 15% dropout rate [22], the total number of study participants will be 926, resulting in 463 participants in each group. In the occurrence of participant withdrawal within 7 days of randomization, replacement participants may be recruited.

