### Statistical analysis

The results of this trial for outcomes will be analyzed based on intention-to-treat (ITT), modified ITT (mITT), and per protocol (PP) approaches, with a primary consideration for mITT results. The ITT group will include all participants who are randomized after satisfying eligibility criteria. The mITT group will include participants who are randomized and who have received the study drugs at least once. The PP group will include participants in the mITT group who have completed the standard treatment for at least 20 of the 24 weeks for the control group or those who have completed the planned treatment for at least 10 of the 12 weeks for the investigational group. A safety analysis will be performed based on the safety group, which will include participants who have been administered with at least one dose of the investigational drugs.

For the primary outcome analysis, the frequency of occurrence of unfavorable outcomes in the control and investigational groups will be analyzed, and the incidence rate of unfavorable outcomes ($${\widehat{P}}_{T}, {\widehat{P}}_{C}$$) and the 95% confidence interval will be estimated. In this non-inferiority test, if the upper limit of the two-sided 95% confidence interval of the difference in incidence of unfavorable outcomes at 18 months between the investigational and control groups ($${\widehat{P}}_{T}-{\widehat{P}}_{C}$$) is less than 6%, it will be concluded that the investigational group is not inferior to the control group.

For the analysis of time to unfavorable outcome, time to culture conversion, and time to recurrence, the median time of each group will be estimated using the Kaplan–Meier method and will be compared with the log-rank test. Treatment success rate and recurrent rate at the end of treatment will be compared with the chi-square test or Fisher’s exact test between the two groups.

Safety will be assessed based on the occurrence of adverse events during the clinical trial period. The frequency and proportion of all adverse events, serious adverse events, and adverse events of grade 3 or higher will be summarized and compared using the chi-square test or Fisher’s exact test.

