## Discussion

The Hi-DoRi-3 is a phase 3 open-label, multicenter, randomized, non-inferiority clinical trial that aims to investigate the effectiveness of a high-dose rifampicin-containing regimen for the treatment of drug-sensitive TB. In this study, the effectiveness and safety of a regimen with a shortened and individualized treatment duration will be compared with the standard 6-month regimen for TB treatment. The three-drug intervention regimen will include high-dose rifampicin (30 mg/kg) with isoniazid and pyrazinamide, which will be administered until culture conversion, followed by 12-week administration of high-dose rifampicin and isoniazid.

In South Korea, the treatment success rate of TB is ~ 90%. While less than 1% of TB patients could not be cured, 5.3–25.2% of TB patients were lost to follow-up [23]. The standard 6-month regimen, comprising four drugs, has remained unchanged for almost 40 years [3]. To enhance compliance and adherence to TB treatment, simple, less toxic, and shorter regimens are needed. With the aim to shorten treatment duration in TB patients, 4-month fluoroquinolone-containing regimens were compared with the standard treatment [7–9]; however, non-inferiority of these regimens was not proven.

For the last ~ 40 years, recommendations for the maximal dose of rifampicin have been confined to 10 mg/kg or 600 mg per day [4, 17]. The peak concentration after ingestion of the currently recommended dose of rifampicin is considered to be well above the minimum inhibitory concentration of *M. tuberculosis* [13]. However, this dose is at the lower end of the dose–response curve, and the drug concentration in *M. tuberculosis* and at the site of infection has not been considered [13]. Increased rifampicin exposure led to higher bactericidal and sterilizing activity for TB according to several in vitro and in vivo studies [24–26]. In human studies, higher doses of rifampicin shortened the time to sputum culture conversion compared with the conventional rifampicin dose [12, 14, 27]. The rate of serious adverse events in patients receiving higher doses of rifampicin was comparable to that in patients receiving the conventional dose [16].

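### Fewer losses in the shorter arm could offset extra relapse in the composite that alone decides non-inferiority, and the planned recurrence tests cannot rule out an excess

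*Protocol article*

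**What the plan says.** The Definitions section builds the primary endpoint as one count: "The sum of treatment failure, recurrence, death during treatment (except for accidents and suicide), loss to follow-up, and withdrawal from the study". Every component carries the same weight; in particular, "loss to follow-up, and withdrawal from the study will be designated as" unfavorable outcomes.

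Under Statistical analysis, the regimen passes if the upper two-sided 95% confidence limit for the difference in that count at 18 months is below 6%; then "it will be concluded that the investigational group is not inferior to the control group". The mITT result has primary consideration, and ITT and per-protocol analyses are also planned. No recurrence or failure result enters the rule.

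Recurrence is a secondary outcome in two forms under Study outcomes: the proportion at 18 months, and the time to recurrence after treatment completion. The time is analyzed by Kaplan–Meier and log-rank. For the proportion, "Treatment success rate and recurrent rate at the end of treatment will be compared with the chi-square test" or Fisher's exact test. The Definitions section, however, places recurrence after the end of treatment.

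The Sample size calculation states that "a 10% unfavorable treatment outcome for the standard treatment (control group) and a 0% difference from the investigational group is assumed". The Discussion gives Korean background: about 90% treatment success, and "While less than 1% of TB patients could not be cured, 5.3–25.2% of TB patients were lost to follow-up".

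**The concern.** Relapse is the main risk of a shortened regimen. A composite that counts loss and withdrawal in full mixes that risk with retention, and retention is something the trial expects to improve: the Background and Discussion argue for shorter treatment because it should help adherence. If it does, a fall in losses can cancel a rise in relapse, and the total will not show it.

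The recurrence analyses would then have to reveal the excess. Both are difference tests without a margin or an interval criterion, so a non-significant result does not show that relapse is acceptably similar. At stake is a non-inferiority statement published beside a reassuring but uninformative p-value for recurrence.

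**Working it through.** **1. The plan's own figure.** Inputs from the Sample size calculation: 10% in both arms, margin 6%, one-sided 2.5%, power 80%.

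n = (1.960 + 0.842)² × (0.10×0.90 + 0.10×0.90) / 0.06² = 392.4, so 393 per group. With 15% dropout, 393/0.85 = 462.4, so 463 per group and 926 in total. The stated figures reproduce. Results below are for 463 and, in brackets, 393.

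**2. How much of the 10% might be loss.** Setting the low end of the national loss range against the assumed rate gives 5.3/10 = 53%. This is only an indication. The upper end, 25.2%, exceeds the whole 10%, and no recurrence or death rate is given.

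**3. Assumed split (not in the documents).** Control: recurrence 2%, other events 8%. Investigational: recurrence 4%, with other events at 6% (full offset), 7% (half offset) or 8% (no offset).

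**4. Probability of declaring non-inferiority.** P = Φ((0.06 − d)/SE − 1.96), with d the true difference in the composite and SE unpooled.

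- Full offset, 10% v 10%: SE = √(0.18/463) = 0.0197; 0.06/0.0197 − 1.96 = 1.08; P = 0.86 (0.80).
- Half offset, 10% v 11%: SE = 0.0202; 0.05/0.0202 − 1.96 = 0.52; P = 0.70 (0.63).
- No offset, 10% v 12%: SE = 0.0206; 0.04/0.0206 − 1.96 = −0.01; P = 0.49 (0.43).

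With no offset, larger excesses are mostly stopped: recurrence 2% v 6% (composite 10% v 14%) passes 0.15 (0.14), and 2% v 8% (10% v 16%) passes 0.025.

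**5. Power of the chi-square test for 2% v 4%.** The pooled proportion is 3%. SE₀ = √(2×0.03×0.97/463) = 0.01121 and SE₁ = √((0.0196 + 0.0384)/463) = 0.01119.

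Power = Φ((0.02 − 1.96×0.01121)/0.01119) = 0.43 (0.38). For 80% power the test would need 1141 per arm.

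**6. Both together.** In a multinomial simulation of the full-offset case, non-inferiority was declared and recurrence was non-significant in 53% (56%) of trials.

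**7. What an interval would show.** For 2% v 4% the half-width is 1.96 × 0.0112 = 2.2 points, so a typical 95% CI is about −0.2 to +4.2 points. A reader would see that an excess of 4 points is not excluded. This ignores the failure component and censoring.

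**8. Would 6% work as a second gate?** For failure or recurrence at 2% v 4%, P(upper limit < 6%) = Φ(0.04/0.0112 − 1.96) = 0.95 (0.91). The gate would let the doubling through.

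**The case against.** - **Recurrence is not left to a chi-square test alone.** A log-rank test is planned too, and the per-protocol set drops participants who fall short of most of their planned treatment, which removes many on-treatment losses. This stands as partial protection. But the log-rank test is also a difference test, and the per-protocol analysis still uses the composite and is not the primary one.
- **The split is assumed.** A reader might infer that the protocol's own figures show the composite to be mostly loss. They do not: the Discussion's figures are national and omit recurrence and death, and the components of the assumed 10% are not given.
- **Masking needs unequal loss.** Both arms are followed to 18 months, so a shorter course shortens only part of the period in which participants can be lost. A full offset is the extreme case.
- **Large excesses would be seen.** A reader might infer that much higher relapse would pass unnoticed. If failure plus recurrence were 1% v 6% and fully offset, non-inferiority would still be declared 86% of the time at 463 per arm, but a chi-square test on that excess would be significant in about 99% of trials. With no offset the composite would pass only about 7% of the time. The exposed range is a moderate excess, such as a doubling from a low rate.
- **Design choice and condensed article.** An all-cause composite is legitimate, and supportive component analyses are often left to the analysis plan. That stands, so the composite is not the fault. The article does, however, fix which recurrence test is used and when. The phrase about the end of treatment may be a slip meant only for treatment success, but as worded it conflicts with the Definitions and Study outcomes sections.

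**Conclusion.** The point holds in a limited form. The decision rule uses only a composite in which loss and withdrawal count in full, and the stated recurrence analyses cannot rule out an excess. Under the assumed split, a fully offset doubling of recurrence is declared non-inferior about 86% of the time (80% at 393), with a chi-square test that detects it less than half the time. With half the offset the figure is 70% (63%), and with none it is 49% (43%).

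The result rests on two assumptions: recurrence near 2% in the control arm, and fewer losses in the shorter arm. The trial's rationale points in the direction of the second, but the documents give no size for it.

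A reader might conclude that the trial cannot answer its question, or that it needs a second pass/fail condition at 6% on failure or recurrence. Neither follows. The composite margin protects well when loss is similar between arms. The documents do not justify 6% for this component, and it would pass the doubling from 2% to 4% about 91–95% of the time.

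Separately, the wording that compares recurrence at the end of treatment conflicts with the definition of recurrence and must be corrected in any case.

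**What to change.** Keep the composite as primary and leave the decision rule unchanged. Under Statistical analysis:

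1. Replace the end-of-treatment chi-square comparison of recurrence with the between-arm difference in 18-month risk of bacteriological failure or recurrence, counted from randomization, with a two-sided 95% CI. Name it the prespecified key supportive analysis, run it in the mITT and per-protocol sets, and report it beside the primary result. Say whether the part of the failure definition based on use of second-line drugs counts. Starting at randomization keeps the arms comparable; time after treatment completion covers completers only, with different lengths of follow-up.
2. Add a sensitivity analysis that varies the assumed risk of failure or recurrence among lost participants, separately by arm. Censoring them assumes that loss is non-informative.
3. Do not add the 6% composite margin as a second pass/fail condition.

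The data are already collected under the visit schedule. The sample size and the power of the primary test do not change. The cost is a protocol and analysis-plan amendment and modest extra analysis. The downside is that the supportive interval may complicate a non-inferiority claim.

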### Investigational group

Participants randomized to the investigational group will be treated with high-dose rifampicin (body weight, dose: < 44 kg, 1200 mg/day; 45–54 kg, 1500 mg/day; 55–64 kg, 1800 mg/day; 65–74 kg, 2100 mg/day; > 75 kg, 2400 mg/day), isoniazid (300 mg/day), and pyrazinamide (body weight, dose: < 50 kg, 1000 mg/day; 50–70 kg, 1500 mg/day; > 70 kg, 2000 mg/day) until culture conversion (liquid medium) is confirmed (Table 2). High-dose rifampicin and isoniazid will be administered until 12 weeks after the date of sputum culture negative conversion. The dosage of rifampicin will be maintained throughout the study duration. Ethambutol will not be included in the initial regimen to reduce the number of pills. However, in the instance that isoniazid or pyrazinamide is discontinued prior to the end of treatment, ethambutol may be added to the treatment regimen if the investigator decides that reinforcement of the drug is necessary. Although temporary use of secondary anti-TB drugs is permitted in the case of adverse events such as liver toxicity, the total duration of use should be less than 4 weeks. If rifampicin is discontinued because of adverse events, the period of discontinuation must also be less than 4 weeks. The study overview is provided in Fig. 1.

**Table 2 Tab2:** Dose and schedule of anti-tuberculous drugs for the investigational group

Drug name	Dose (body weight)	Administration method
Isoniazid	300 mg/day	once a day before meal
Rifampicin	1200 mg/day (< 44 kg) 1500 mg/day (45–54 kg) 1800 mg/day (55–64 kg) 2100 mg/day (65–74 kg) 2400 mg/day (> 75 kg)	once a day before meal
Pyrazinamide	1000 mg/day (< 50 kg) 1500 mg/day (50–70 kg) 2000 mg/day (> 70 kg)	once a day after meal

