^h^ The date of the end of treatment is determined according to the time of culture conversion to negative. A visit every 4 weeks until EOT and every 3 months after EOT. The test is not performed after EOT

^i^ If the 78-week visit (EOS) after randomization arrives earlier than the EOT + 12 M visit, the EOT + 12 M visit is omitted, and the EOS visit proceeds

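### On-treatment culture reversion enters no component of the primary outcome, and non-conversion is judged over a window that differs between the arms

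*Protocol article*

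**What the plan says.** All outcome definitions are in the Definitions section of the protocol article.

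- **Unfavorable outcome** is a closed list: "The sum of treatment failure, recurrence, death during treatment (except for accidents and suicide), loss to follow-up, and withdrawal from the study".
- **Treatment failure** has two routes. The first is non-conversion: "Treatment failure will be defined as participants who fail to achieve culture conversion during treatment period". The second is taking second-line drugs beyond 4 weeks.
- **Recurrence** requires "presence of *M. tuberculosis* in sputum cultures for two or more times after the end of treatment".
- **Culture reversion** is defined separately, when *M. tuberculosis* is "re-cultured two or more times following a negative culture conversion, this will be termed culture reversion". The term appears in none of the components above.
- **Treatment success**, a secondary outcome: "Treatment success is defined as achieving negative culture conversion and maintaining negative cultures till the end of treatment".

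The treatment period is set differently in the two arms. For the investigational arm, the Investigational group section states: "High-dose rifampicin and isoniazid will be administered until 12 weeks after the date of sputum culture negative conversion", and footnote h of Table 4 adds: "The date of the end of treatment is determined according to the time of culture conversion to negative". No maximum is given. For the control arm, the Control group section gives a total of 6 months, while footnote h of Table 3 leaves the end date to standard-of-care guidelines. Both tables list on-treatment visits up to week 32.

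The primary outcome is the proportion unfavorable at 18 months after randomization (Study outcomes).

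**The concern.** Reversion on treatment and slow or absent conversion are bacteriological events that a shortened, three-drug, conversion-timed regimen has to be tested against. The plan anticipates reversion: it defines it, and Tables 3 and 4 call for susceptibility testing of reverted cultures. Yet no outcome component counts it as such.

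Non-conversion is a component, but in the investigational arm the window in which it is judged is fixed by conversion itself. A criterion tied in one arm to the event it is meant to detect, and in the other to a nominal duration, does not measure the same thing in both arms. The primary analysis is a difference in proportions set against a 6-point margin, so each net point of failure uncounted in one arm moves that difference by one point.

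**Working it through.** **1. Tracing a reverter through the definitions.** Take a participant who converts, grows *M. tuberculosis* twice while still on treatment, stays on first-line drugs, and has fewer than two positive cultures after treatment.

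| Component | Met? | Reason |
|---|---|---|
| Failure, non-conversion | No | Conversion was achieved |
| Failure, second-line drugs for more than 4 weeks | No | Stays on first-line drugs |
| Recurrence | No | The positives fall before the end of treatment |
| Death on treatment, loss to follow-up, withdrawal | No | None occurred |
| Treatment success (secondary) | No | Negative cultures were not maintained |

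The participant is not a success and not unfavorable.

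**2. Non-conversion by arm.** In the investigational arm the planned end of treatment is the conversion date plus 12 weeks, so treatment that ends as planned always ends in a converter. The criterion can be met only by stopping early without conversion, or by having no conversion by month 18. In the control arm the period is nominally 6 months and is not set by conversion. A participant who first converts after the control period has ended is a failure in control; one converting at the same time in the investigational arm, still on treatment, is not.

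**3. Direction of the reversion gap.** Suppose conversion at week 8 in both arms. Investigational treatment ends at week 8 + 12 = 20. Taking 6 months as 24 to 26 weeks, control has 16 to 18 weeks of treatment left. Two positive cultures between weeks 20 and 24 are recurrence (counted) in the investigational arm and on-treatment reversion (not counted) in control. For such participants the gap works against the investigational arm.

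**4. The plan's own figure.** Inputs from Sample size calculation: 10% unfavorable in each arm, margin 6 points, one-sided 2.5%, power 80%, dropout 15%.

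n = (1.960 + 0.842)² × (0.10 × 0.90 + 0.10 × 0.90) / 0.06² = 392.4, so 393 per arm. With dropout, 393 / 0.85 = 462.4, so 463 per arm and 926 in total. Both figures reproduce.

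**5. Sensitivity of the conclusion.** Let r be the net proportion of investigational-arm failures left uncounted. The documents give no value, so r is assumed. Put the full difference exactly at the margin (control 10%, investigational 16%). The counted investigational rate is 16% − r, and

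P(declare non-inferiority) = Φ( r / SE − 1.960 ), with SE = √{[0.10 × 0.90 + (0.16 − r)(0.84 + r)] / n}.

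| r (assumed) | 393 per arm | 463 per arm |
|---|---|---|
| 0 | 2.5% | 2.5% |
| 0.5 points | 4.0% | 4.2% |
| 1 point | 6.2% | 6.7% |
| 2 points | 13.7% | 15.3% |

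For r = 1 point at 393 per arm: SE = √[(0.0900 + 0.1275)/393] = 0.0235, and 0.01/0.0235 − 1.960 = −1.535, giving 6.2%. In participants, 0.5, 1 and 2 points are about 2, 5 and 9 of 463.

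**6. Power cost of counting more events.** If the unfavorable rate rises by 1 point in both arms to 11%, then at 393 per arm SE = √(2 × 0.11 × 0.89 / 393) = 0.0223 and power = Φ(0.06/0.0223 − 1.960) = 76.7%, against 80.1% at 10%. Restoring 80% would need 427 per arm before dropout.

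**The case against.** Several points on the other side stand.

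- **Other components catch some reverters.** Second-line drugs for more than 4 weeks, death on treatment, loss to follow-up, withdrawal, or two positives after treatment each make a reverter unfavorable. The uncounted group is only what remains. The second-line route is a weak backstop, though: it depends on prescribing by physicians who know the allocation.
- **A reader might infer that investigational participants can never fail by non-conversion.** The text does not support that. Early stopping without conversion, or no conversion by month 18, meets the wording.
- **A reader might also infer that every control participant converting after 6 months is a failure.** That does not follow either. Footnote h of Table 3 ties the control end date to guidelines, and visits run to week 32, so some control participants may convert late while still on treatment.
- **A bias in one direction, toward non-inferiority, is tempting but not shown.** The week-8 example shows the reversion gap can run the other way.
- **The size is assumed.** The only related figure is in the Discussion, that fewer than 1% of South Korean TB patients could not be cured. It is national and does not describe this regimen.
- **The article is condensed.** The full protocol may set a maximum duration or a failure time point, which lowers confidence in the non-conversion part. It does not rescue the reversion part, because the article states the outcome definitions themselves and they leave the gap.

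**Conclusion.** The concern holds in a limited form. As written, some participants with bacteriological failure on treatment are not counted as unfavorable, although the plan's own success definition excludes them from success. Bacteriological failure is also assessed differently in the two arms. The non-conversion element tends to favor the investigational arm; the net direction of the reversion gap is uncertain because treatment lengths differ.

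The size cannot be established from the documents. The rise in false non-inferiority risk from 2.5% to roughly 4% to 15% rests on an assumed 0.5 to 2 net points uncounted in the investigational arm, a true difference exactly at the margin, and a 10% control rate. It shows sensitivity and is not an estimate of bias.

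A secondary matter is that conversion requires at least one negative culture, so a participant who never produces sputum on treatment would be a failure on a literal reading. No direction of bias has been shown for this, and it does not carry the point.

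**What to change.** For the primary endpoint, in both arms:

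1. Add confirmed on-treatment culture reversion, using the existing two-or-more definition, to the components of the unfavorable outcome.
2. Assess non-conversion at one common time from randomization instead of over the treatment period. Weeks 24, 28 and 32 already appear in both visit tables; the choice is for the trial team.
3. Reconcile the Control group and Investigational group sections, footnote h of Tables 3 and 4, and the Definitions section on what the treatment period is in each arm. This concerns endpoint classification and implies no particular treatment duration.

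The cost is a wording change in the protocol and the analysis plan; the cultures are already scheduled. The unfavorable rate may rise slightly. One extra point in both arms would lower power at 393 per arm from about 80% to 77%.
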